## Abstract

**Background:**

We describe the study design, procedures, and development of the risk counseling protocol used in a randomized controlled trial to evaluate the impact of genetic testing for diabetes mellitus (DM) on psychological, health behavior, and clinical outcomes.

**Methods/Design:**

Eligible patients are aged 21 to 65 years with body mass index (BMI) ≥27 kg/m^2^ and no prior diagnosis of DM. At baseline, conventional DM risk factors are assessed, and blood is drawn for possible genetic testing. Participants are randomized to receive conventional risk counseling for DM with eye disease counseling or with genetic test results. The counseling protocol was pilot tested to identify an acceptable graphical format for conveying risk estimates and match the length of the eye disease to genetic counseling. Risk estimates are presented with a vertical bar graph denoting risk level with colors and descriptors. After receiving either genetic counseling regarding risk for DM or control counseling on eye disease, brief lifestyle counseling for prevention of DM is provided to all participants.

**Discussion:**

A standardized risk counseling protocol is being used in a randomized trial of 600 participants. Results of this trial will inform policy about whether risk counseling should include genetic counseling.

**Trial registration:**

ClinicalTrials.gov Identifier NCT01060540

## Background

Genetic testing has become an increasingly viable option for conveying the risk of developing complex chronic diseases [1]. Genetic testing for this purpose currently is not a routine part of primary care. Barriers may include a lack of resources for testing, a lack of genetic counselors to deliver the results, and uncertainty about whether knowing genetic risk prompts risk reduction behaviors [2]. Evidence of the clinical utility of providing genetic testing results is needed to inform policy regarding the use of genetic testing for complex chronic diseases in clinical care.

Diabetes mellitus (DM) is an ideal prototype disease for examining this issue for several reasons. First, DM is a highly prevalent and costly chronic disease that results in debilitating microvascular and macrovascular complications and impaired quality of life [3,4]. Second, genetic abnormalities in complex chronic diseases such as DM involve multiple genes such that testing determines disease risk [5]. This is in contrast to Mendelian disorders, which result from a mutation in a single causative gene and for which single-gene tests determine, definitively, the presence or absence of disease, regardless of lifestyle choices. Third, much is known about the environmental and genetic contributors to the development of DM, and the evidence suggests that behavior change is the best way to prevent its development, even when gene polymorphisms are present [6].

We are conducting a randomized controlled trial (RCT) to examine the comparative effectiveness of risk counseling using conventional risk factors for DM versus counseling that additionally includes genetic testing results. In this article, we report on the study design, procedures, and development of the counseling protocol.

## Methods/Design

### Study design and overview

The ongoing study is a two-arm RCT to determine the effect of genetic testing for DM on clinical outcomes and health behaviors. At baseline, participants provide written informed consent, information for conventional risk assessment, blood samples for fasting plasma glucose (FPG) and possible genetic testing, and baseline clinical and health behavior outcomes (Figure 1). Eligible participants are then randomized to receive conventional risk plus genetic test result counseling (CR + G) or conventional risk plus control eye disease counseling (CR + E), stratified by family history (unknown/low vs. moderate/high) and body mass index (BMI; < 35 vs. ≥ 35 kg/m^2^). Two to 4 weeks following baseline, all participants return for a risk counseling visit with a genetic counselor that does (CR + G) or does not (CR + E) include delivery of genetic test results and associated counseling. Psychological outcomes are assessed immediately following counseling and at 3 and 6 months. Behavioral and clinical outcomes are assessed at 3 and 6 months, with 3 months as the primary endpoint.

**Figure 1 F1:**
[figure not shown]
Study overview.

### Study population and recruitment

Participants are recruited from the Durham Veterans Affairs Medical Center (VAMC) and satellite clinics. Ethical approval was obtained from the Institutional Review Board and Research and Development committees at the Durham VAMC. Eligibility is confirmed by an electronic data pull followed by a screening telephone call and a baseline visit (see Table 1 for eligibility criteria). A recruitment letter is mailed to patients meeting inclusion criteria who have a clinical appointment in the next 3 weeks. If patients do not opt out of the study by calling a toll-free number, a research assistant (RA) contacts them by phone within 2 weeks to describe the study, assess interest, and administer a cognitive screen [7]. Patients may also self-refer in response to flyers posted in the medical center. Interested and eligible patients are then scheduled for the baseline study visit. Patients receive reminder letters with fasting instructions 1 week before their scheduled appointments and reminder phone calls the day before their appointments.

**Table 1 T1:** Eligibility criteria and method of ascertainment

	**Criterion**	**Method**
Inclusion criteria	Age 21–65 years	Electronic data pull
	Body mass index ≥ 27 kg/m^2^	Electronic data pull (≥ 26 kg/m^2^ to allow for error), screening telephone call, and confirmed at baseline visit
Exclusion criteria	Diagnosis of diabetes mellitus	Electronic data pull, confirmed in telephone call
	Fasting plasma glucose ≤ 125 mg/dl on more than one occasion	Electronic data pull
	Hemoglobin A1c >7%	Electronic data pull
	Taking diabetes medication	Electronic data pull, confirmed in telephone call
	Intentional weight loss of at least 5 lbs in previous 3 months	Screening telephone call
	Enrolled in a research study or any program focused on lifestyle changes	Screening telephone call
	Unable to provide informed consent or answer survey questions unassisted	Screening telephone call
	Residing in nursing home or receiving home health care	Screening telephone call
	At least 1 error on a validated 6-item screen for cognitive impairment [7]	Screening telephone call
	Fasting plasma glucose ≤ 125 mg/dl at baseline	Baseline visit

### Baseline visit

At the baseline visit, an RA describes the study, reviews the risks and benefits of genetic testing, and reviews the randomization process. After any questions are addressed, participants provide written informed consent. Participants are asked not to obtain genetic testing from outside resources while enrolled in our study. Age, sex, race, family history, weight, and height are collected for use in calculating cumulative lifetime risk for DM. History of DM is obtained for first- and second-degree relatives. Upon confirmation that patients have fasted for 12 h, blood is drawn for FPG, fasting insulin, and possible genetic testing. Participants complete a measure of numeracy [8], then the RA administers all other measures orally. Participants receive $25 for this 1-h visit. Final study eligibility is determined based on the baseline FPG results, usually available within 24 h.

### Randomization

Participants are randomized to the CR + G versus the CR + E arms in blocks within four strata defined by weight status (BMI <35 kg/m^2^ vs. ≥ 35 kg/m^2^) * family history of DM (unknown/low vs. moderate/high). We wanted to ensure balance in each arm on BMI status as weight trajectories, and adherence to recommendations may differ depending on severity of obesity. We also wanted to ensure balance on family history of DM in each arm as individuals with a strong family history may be more likely to engage in preventive lifestyle changes [9]. The project coordinator enters the values of the stratification variables and FPG into the study database, and the randomly assigned study arm is returned for eligible patients. Then, due to budget constraints, only blood samples for CR + G participants are sent for genetic testing.

Only the project coordinator and Master’s-level statistician have access to the randomization section of the study database. RAs are blind to arm assignment, and arm assignment is not revealed to participants or the genetic counselor until during the counseling session, after the conventional risk counseling has been delivered. Because randomization occurs prior to the genetic counseling session (to determine which blood samples will be extracted for genetic testing), participants are considered randomized whether or not they attend the counseling appointment and will be analyzed in an intent-to-treat manner.

### Genetic testing

To date, single nucleotide polymorphisms (SNPs) that have been associated with DM are weakly associated, typically yielding odds ratios (OR) <2.0, although combinations of multiple SNPs have resulted in larger ORs [10]. We are examining how genetic information influences health behaviors and hypothesize that even markers with small ORs may affect health behaviors. We selected 3 DM-related genes (TCF7L2, PPARg, and KCNJ11) in which to test SNPs because, when we designed this study, they were among the most studied SNPs, even in populations of varying ethnicities [10].

The Duke Clinical Molecular Diagnostics Laboratory is performing the genetic testing. The regions of the KCNJ11, PPARG, and TCF7L2 genes, which encompass the desired single nucleotide polymorphisms of interest [Rs5219T > C, Rs1801282C > G, Rs7903146C > T, respectively], are amplified using three primer pairs. Purified genomic DNA is used for polymerase chain reaction (PCR). The primers used in the PCR reactions contain M13 universal primer “tails” at their 5′ ends and have 3′ ends that are homologous to their genomic target sequence. The resulting PCR products are treated with an exonuclease/ phosphatase mixture (ExoSAP-IT: USB Corporation) to remove excess PCR primers and nucleotides. These purified DNA amplicons are then sequenced using universal M13 forward and reverse primers [M13 Forward (17 bp) and M13 Reverse (17 bp)] and the Big Dye Terminator v3.1 Cycle Sequencing Kit (Applied Biosystems). These products are then purified with the Big Dye XTerminator Purification Kit (Applied Biosystems) and resolved using the ABI 3130xl Genetic Analyzer. Data are analyzed using the ABI Data Collection software v3.0, Sequencing Analysis software v5.2 and SeqScape software v2.5. Sequences are compared to the reference DNA sequence (GenBank accession: K:NT_009237.18, P:NT_022517.18, T:NT_030059.12).

### Risk stratification

We provide patients with risk estimates for up to four different DM risk factors (lifetime risk based on age, sex, race, and BMI; risk based on family history; risk based on FPG level; and, for those randomized to the CR + G group, risk based on genetic testing for 3 DM-related genes) rather than one global DM risk value because there is no well-validated algorithm that incorporates various DM risk factors into a single prediction score similar to the Framingham risk score for cardiovascular disease risk. We categorize participants’ risk into three levels based on validated algorithms (low, moderate, or high; Table 2) to provide patients with a means of “fairly” comparing their risk across the different measures given the fact that the reference groups for the numerical risk categories often differ (e.g., lifetime DM risk based on BMI, race, sex, and age being presented as a percentage versus DM risk based on FPG being presented as an odds of developing DM in the next 5 years). Furthermore, numerical risk information tends to be poorly understood by patients [11], particularly when information is unfamiliar and presented in isolation [12,13]. Rather, people tend to focus more on the gist of risk information [14].

**Table 2 T2:** Low, moderate, and high-risk values for each risk category

**Risk category**	**Low risk**	**Moderate risk**	**High risk**
**population-based risk**	**<20%**	**20-40%**	**>40%**
Family history	Only (1) one second-degree relative with DM from one or both sides of family; or no family history of DM	Only (1) one first- and one second-degree relative with DM from same lineage; (2) one first-degree relative with DM; (3) mother and father with DM; or (4) two second-degree relatives from same lineage with DM	At least (1) two first-degree relatives with DM from same lineage; (2) one first- and two second-degree relatives with DM from same lineage; or (3) three second-degree relatives with DM from same lineage
Fasting plasma glucose (FPG)	<100 mg/dl	100-109 mg/dl	110-125 mg/dl*
Copies of high-risk alleles from TCF7L2, PPARg, KNCJ11 (possible range 0–6)	0-2	3	4-6

*** Participants with FPG >125 mg/dl are excluded.

Population-based risk estimates are taken from lifetime risk tables based on age, sex, race, and BMI [15]. We classified <20% lifetime risk as low, 21-40% as moderate, and >40% as high. Family history of DM is based on first- and second-degree relatives, and classification into risk levels is based on a published algorithm [16]. Although the American Diabetes Association guidelines consider prediabetes present when FPG >100-125 mg/dl, analyses indicate a high false-positive rate for values between 100 and 109 mg/dl [17]. Therefore, participants are classified according to whether their FPG is <100 mg/dl (low), 100–109 mg/dl (moderate), or 110–125 mg/dl (high). Participants with baseline FPG >125 mg/dl become ineligible and are encouraged to follow-up with their primary care provider. Based on the distribution of the possible combinations of the high-risk alleles that we are testing in a previous study [10], we designated 0–2 high-risk alleles as low risk, 3 as moderate, and 4–6 as high risk.

**Figure 2 F2:**
[figure not shown]
Sample graphs for lifetime risk, family history, fasting plasma glucose, and genetic testing.

At the end of the counseling session, [name] conducted qualitative interviews to examine participants’ interpretation of the information, solicit feedback on the counseling protocol, and evaluate different pictorial presentations of personalized risk information. Specifically, participants viewed a pie graph, a vertical bar graph, a horizontal bar graph, and a speedometer, all in black and white and in color versions (low risk = green, moderate risk = yellow, high risk = red). Participants were asked to compare the graphs, indicate which best conveyed risk level, and for their interpretation of the descriptors and colors. Participants preferred the vertical thermometer, indicated that the colors aided in interpretation of the risk level, and indicated that the colors matched the descriptors.

#### Genetic risk (CR + G)

The genetic counselor provides a brief review of genetics and indicates that studies have linked several genes to the development of DM. The genetic counselor further indicates that genetic testing for DM does not yield definitive risk estimates, but rather that it supplements the risk information already considered with the other three risk categories. Next, the genetic counselor provides participants with their personal genetic testing results in a manner similar to the other risk estimates using a vertical thermometer bar graph (last graph in Figure 2). The genetic counselor emphasizes that we tested only three of several genes that are associated with increased DM risk and that lifestyle modification can prevent or delay the onset of DM even if genetic results indicate an increased risk.

#### Control counseling (CR + E)

To ensure that the control arm (CR + E) receives equal duration of genetic counselor contact, information is reviewed for age-related macular degeneration, cataracts, and glaucoma. We chose this control topic because the lifestyle modifications recommended to prevent these eye diseases overlap little with those recommended to prevent DM. Additionally, although DM is a risk factor for eye disease, we chose eye disease topics that would not emphasize this risk so that the information presented would be unlikely to add to control participants’ motivation to prevent DM. Participants receive information about risk factors, screening, and behaviors to reduce their risk for the three eye diseases, although no individualized risk information is presented. Ten pilot participants completed a risk counseling session with eye counseling instead of genetic counseling to ensure that participants understood the information and to match the duration of the eye disease counseling to the duration of the genetic counseling (approximately 10 min). Thus, any difference between arms could not be attributed to the increased amount of time spent with participants in the CR + G arm, but rather the content of the genetic counseling.

#### Lifestyle counseling (both arms)

Following genetic or eye disease counseling, the genetic counselor engages participants in brief lifestyle counseling. The counselor informs participants that lifestyle changes can help ameliorate risk, even in the presence of family history or genetic abnormalities. Using a semi-structured script that operationalizes some basic principles of motivational interviewing, the genetic counselor encourages participants to set physical activity and/or dietary intake goals, with an emphasis on simple, short-term, and measurable goals [6]. Goals are recorded on a sheet to take home, and participants are encouraged to review their progress monthly and adjust goals accordingly. Participants are provided with a summary statement containing their risk information, including genetic testing results if in the CR + G arm; the National Institutes of Health *Game Plan* resources, which are based on the Diabetes Prevention Program and provide comprehensive information about DM and tools for adopting prevention behaviors; an informational pamphlet on DM that we created; and a list of resources available at VA, including website addresses. Participants in the CR + G arm also receive the NHGRI publication *A Guide to Your Genome* to aid in genome science education and comprehension of genetic information. Participants receive $25 for this visit, which can take up to 1.5 h.

### Measures

Demographics are assessed at baseline by an RA. Psychological outcomes are assessed by the genetic counselor immediately following the risk counseling. The remaining outcomes are assessed by a blinded RA at 3 and 6 months, with 3 months as the primary endpoint. Participants receive $25 for the 3- and 6-month outcome visits.

#### Primary outcome

The primary outcome is weight because it is sensitive to lifestyle modifications [19] and is highly correlated within an individual over time, even in studies of intensive weight loss interventions [20]. Weight change was more influential than physical activity level or dietary fat intake for the prevention of DM in the Diabetes Prevention Program [21]. Body weight is measured on a standardized digital scale, with participants wearing light clothing and with accessories and shoes removed.

#### Psychological outcomes

Likelihood is assessed with the item, “What are your chances of getting type 2 diabetes in your lifetime?” (1 = *definitely will not get diabetes* to 7 = *definitely will get diabetes)*. The Brief Illness Perception Questionnaire measures dimensions of illness captured by the Common Sense Model, including consequences, timeline, personal control, treatment control, identity, concern, understanding, emotional response, and causal attributions [22]; items are modified to focus on developing DM in the future as opposed to now. Readiness to change diet and increase physical activity is assessed with single items [23]. Self-efficacy to follow a diet is assessed with the revised Eating Self-Efficacy Scale [24]. Self-efficacy to engage in physical activity is assessed with the Self-Efficacy for Exercise scale [25]. Intentions to modify dietary intake and increase physical activity are assessed with seven semantic differential items.

#### Reactions to genetic testing

The Multidimensional Impact of Cancer Risk Assessment Questionnaire is administered in the CR + G arm only at 3 and 6 months to assess the psychosocial impact of receiving a genetic test result and was adapted for DM [26].

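### A questionnaire given only in the CR + G arm at the 3- and 6-month time points undermines the stated blinding of the research assistant who assesses outcomes then

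*Protocol article*

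**What the plan says.** Three statements in the protocol article bear on this.

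- *Randomization* states that "RAs are blind to arm assignment". It limits knowledge of the allocation: "Only the project coordinator and Master’s-level statistician have access to the randomization section of the study database". Participants and the genetic counselor learn the arm during the counseling session.
- *Measures* assigns demographics at baseline to an RA and the psychological outcomes straight after counseling to the genetic counselor. It then says: "The remaining outcomes are assessed by a blinded RA at 3 and 6 months, with 3 months as the primary endpoint".
- *Reactions to genetic testing*, a subsection of *Measures*, describes a psychosocial questionnaire adapted for diabetes, on how getting a genetic result affected the participant. It "is administered in the CR + G arm only at 3 and 6 months".

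The mode of administration is described only for the first visit. Under *Baseline visit*, participants complete a numeracy measure, "then the RA administers all other measures orally".

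**The concern.** The questionnaire asks about something that happened in one arm only, and it falls at the time points at which the assessor is supposed to be blind. Being told to give it identifies a CR + G participant. Its absence identifies a CR + E participant. The assessor therefore need not see the randomization database to learn the arm.

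Participants already know their arm by the 3-month visit, so assessor blinding is the main protection left there against differential measurement. The secondary hypotheses include physical activity and caloric intake at 3 and 6 months, and both come from questionnaires. If an RA reads such items aloud while knowing the arm, prompts and clarifications can differ between arms without anyone intending it. Readers of the results would also rely on a claim of blinded assessment that the described procedures do not clearly deliver.

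**Working it through.** No figure in the plan depends on this point, so the check is a comparison of the sections.

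1. **Who is at the follow-up visits?** *Measures* names one assessor for 3 and 6 months, a blinded RA, and gives that person all outcomes not already assigned. *Study design and overview* repeats the psychological outcomes at 3 and 6 months. The counselor's role is limited to one occasion: "Psychological outcomes are assessed by the genetic counselor immediately following the risk counseling". The follow-up psychological scales therefore also appear to fall to the RA.
2. **Who gives the arm-specific questionnaire?** Its own subsection does not say. It is listed among the measures and has the same timing, so it falls naturally within the remaining outcomes. No other administrator is named. That the RA gives it is a strong inference.
3. **Is there a safeguard?** The article mentions no sealed form, separate mailing, filler version for CR + E or rule that the questionnaire comes last.
4. **What follows?** On this reading the RA learns the arm at the 3-month visit, in both arms, by the presence or absence of the form.
5. **Which outcomes are exposed?**
   - *Weight*: "Body weight is measured on a standardized digital scale", under a fixed rule on clothing and shoes. There is little room for assessor influence.
   - *Fasting glucose, insulin and HOMA-IR*: laboratory values and a calculation from them. There is little room here either.
   - *Diet*: the food frequency instructions ask participants to mark items themselves, which suggests self-completion. It is exposed only if the RA reads it aloud.
   - *Physical activity and psychological scales at follow-up*: self-report, and the most exposed if the oral mode used at baseline continues.
   - *Perceived risk immediately after counseling*: assessed by the counselor, who knows the arm by then. This point does not bear on it.
6. **Does order within the visit matter?** Yes, and it is not stated. If the questionnaire came after everything else, all 3-month measures would be taken before the RA learned the arm. The 6-month measures would still be exposed if the same RA saw the participant again or had the 3-month forms to hand.

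**The case against.** The strongest reply is that the sections are under-specified, not incompatible. The project coordinator knows the allocation and could prepare or give the form without telling the RA, and nothing in the article excludes this. A journal article also commonly leaves staffing, mode and order of forms to the full protocol or a procedures manual, which is not shown and may already settle the matter. The 6-month concern needs a further condition, since the article does not say that the same RA sees a participant twice.

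Much of this stands. A reader might infer that the blinding cannot possibly hold. The document does not support that, because a coordinator-run route is compatible with every sentence in it. It is also fair that oral administration is stated for baseline only.

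The reply does not remove the point. The article does more than omit a detail: it claims blinded assessment, and it also places an arm-revealing form among the measures at the same time points. On the natural reading these pull against each other, and the published text offers nothing to reconcile them.

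**Conclusion.** The concern holds in limited form, with moderate severity. As described, the arm-only questionnaire would reveal the arm to the RA whom the article calls blind. This rests on the inference that the RA gives the form. The practical exposure is mainly in RA-administered self-reports. At 6 months it extends to measures taken by an RA who gave the earlier form or can see it.

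A reader might go further and infer bias in the primary outcome, weight at 3 months. The plan's own inputs under *Power and sample size considerations* allow an illustration: SD 55 lb, correlation 0.90, and 300 × (1 − 0.10) = 270 analyzed per arm.

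- SE of the difference = 55 × √(1 − 0.90²) × √(2/270) = 23.97 × 0.0861 = 2.06 lb.
- With a systematic bias *b* between arms, the two-sided type I error is 1 − Φ(1.96 − *b*/SE) + Φ(−1.96 − *b*/SE).
- *b* = 1 lb gives about 7.7%, and *b* = 2 lb gives about 16%.

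The arithmetic is right, but the biases of 1 and 2 lb are invented inputs. Nothing in the document supports them. A 2-lb bias would be a third of the 6-lb target difference and would have to arise systematically on a digital scale. These figures therefore do not measure the problem. The size of any bias is unknown, and a material threat to the primary endpoint is not shown.

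**What to change.** Take the questionnaire out of the blinded RA's hands. Either of two routes would do:

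- The project coordinator, who already knows the allocation, mails it or gives it by phone after the visit.
- Every participant receives an identical sealed envelope for self-completion at the end of the visit, with filler items in CR + E. It goes back sealed to the coordinator, and the RA does not open it.

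In either case, state that weight and all other outcomes are completed first, and keep the completed forms away from the RAs before the 6-month visit. If a safeguard of this kind is already in place, one sentence under *Reactions to genetic testing* saying who gives the form, how and when would settle the point. If neither route is adopted and no safeguard exists, qualify the blinding statements under *Randomization* and *Measures*.

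The cost is small. Existing staff can do it. The envelope route adds a few minutes to the visit, and either route may leave some forms missing on an instrument that carries no stated hypothesis under *Primary analysis* or *Secondary analyses*.
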